### Data collection

Data collection is performed using a web-based case report form (electronic CRF or eCRF). Basic data on patient’s general history and specific fertility history are obtained from the out-patient clinic chart. Characteristics of the initial treatment as well as characteristics of the FET treatment are also noted.

For the cost-efficiency study patients are invited to answer a web-based questionnaire after completing treatment.

### Interventions

#### NC-FET (intervention 1)

Patients allocated to intervention 1 will undergo their FET in a natural cycle. Starting on day 10, 11 or 12 of their cycle regular ultrasonic evaluation of the endometrium thickness and mean diameter of the dominant follicle is performed. When the endometrium is 6 mm or more and the diameter of the dominant follicle is 16-20 mm a blood sample is taken (for blinded analyses of progesterone and LH levels) and ovulation is induced using hCG injection (pregnyl 5000 IE, MSD USA or ovitrelle 250 μgram, Serono Benelux bv, Germany). Thawing and transferring is performed subsequently according to local protocols. A maximum of two embryos will be transferred.

If during ultrasonic evaluation no follicle is visible ovulation is deemed to have occurred. In this event no thawing or transferring will take place. This cycle is regarded a drop-out. Further treatment can be conducted according to local protocols (Figure
2).

**Figure 2 F2:**
[figure not shown]
Flowchart natural cycle.

#### AC-FET (intervention 2)

If patients are allocated to intervention 2, an artificial cycle FET will be performed. From day one of the cycle patients commence oral estradiol (progynova, Bayer, Germany) 2 mg three times daily. After 11, 12 or 13 days an ultrasound is performed. If no leading follicle is present and the endometrial thickness is ≥ 8 mm, micronized progesterone (utrogestan Besins International, Belgium) is added to the regime and thawing and transferring is commenced 4 or 5 days later according to the stage of cryopreservation
[20].

If the endometrial thickness is less than 8 mm, the progynova dose is raised to 2 mg 4 times daily for 7 days. After a week the endometrium is checked once again. When the endometrium thickness is >8 mm and no dominant follicle (≥ 14 mm) is present, utrogestan can be added and thawing and transferring is performed according to local protocols. A maximum of two embryos will be transferred.

If a follicle is visible during ultrasound, serum luteinizing hormone (LH) and progesterone levels are determined. If these are raised, (serum LH ≥ 13 E/l or progesterone ≥ 15 nmol/l) luteinization of the follicle is considered to have taken place and because of the associated diminished pregnancy rates, thawing and transferring will not be performed. If serum levels are below the above mentioned levels thawing and transferring can be performed according to local protocol (Figure
3).

**Figure 3 F3:**
[figure not shown]
Flowchart artificial cycle.

Embryo quality is recorded according to study criteria. These criteria can be used beside clinics’ own criteria. The criteria for embryo quality are based on the consensus between the largest participating centers.

### Statistical analysis

#### Sample size and power considerations

Live birth rates in FET treatment in the Netherlands are, on average, 20% per cycle. The minimal clinical important difference (MCID) could not be based on literature concerning FET treatment alone. Based on other studies within fertility care a consensus of a MCID of 7,5% was adapted. This clinical important difference compares to a one sided hypothesis test with a 0.025% significance level with a null hypothesis of AC-FET being inferior to NC-FET. Using a two-sided alpha of 5% and 80% discriminating capacity we calculated that 1150 patients have to be enrolled in this study. All patients will participate with one cycle only.

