**Methods and design:**

In this randomized, multi-centre, non-inferiority trial we aim to test the hypothesis that there is no significant difference in live birth rates between patients undergoing NC-FET versus AC-FET. The primary outcome will be live birth rate per embryo transfer procedure. Secondary outcomes will be ongoing and clinical pregnancy rate, cancellation rate, (serious) adverse events and cost-efficiency. Based on a live birth rate of 20% and a minimal clinical important difference of 7,5% (one-sided alpha 2,5%, beta 20%) a total of 1150 patients will be needed. Analyzes will be performed using both per protocol as well as intention to treat analyses.

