## Background

In Vitro Fertilization (IVF) or Intra Cytoplasmatic Sperm Injection (ICSI) treatment cycles often produce more embryos than can be transferred during the fresh treatment cycle. Moreover, in some patients embryo transfer is postponed for medical reasons (e.g. ovarian hyperstimulation syndrome). Cryopreservation of these embryos provides both physicians and patients a safe, successful and presumably cost-efficient option
[1-3]. Recent development and implementation of single embryo transfer strategies in IVF and IVF -ICSI programs has increased the importance of successful frozen thawed embryo transfer (FET) programs. Critical for a successful FET program is synchronization between the endometrial development and the embryo
[4-7]. To achieve this, FET requires extensive preparation, timing and planning. In recent years, several methods for endometrium preparation have been developed.

In natural cycle FET (NC-FET) planning of embryo thawing and transfer requires the identification of a period of optimal receptivity
[4-7]. This putative ‘window of implantation’ starts shortly after ovulation. If an embryo is transferred within this window, the chances of conceiving are greater
[4-6]. Planning NC-FET can either be done based on recognition of the LH surge that precedes ovulation (using serum or urine LH monitoring) or by triggering ovulation (sometimes referred to as modified NC-FET). Using modified NC-FET, the development of the dominant follicle is closely monitored by regular ultrasonic evaluation. On reaching a diameter of 16-20 mm human chorionic gonadotrophin (hCG) is administered and ovulation takes place approximately 36 h later. Embryo thawing and transferring can be planned accordingly. Despite ultrasonic monitoring, spontaneous ovulations do occur. In such an event the start of the window of implantation cannot be estimated accurately. Since identification of the onset of the window of implantation is mandatory for further timing of FET, cycles with spontaneous ovulation are usually cancelled. To minimize cancellation, patients are required to visit their clinic several times which is time consuming and expensive. In NC-FET cycles, 5-6% of all patients have insufficient development of the dominant follicle and/or endometrium thickness and treatment has to be cancelled

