### Primary and secondary endpoints

The primary endpoint is live birth rate per FET. Secondary endpoints are cancellation rate, clinical pregnancy rate, ongoing pregnancy rate (all per FET), endometrium thickness during transfer and (serious) adverse events. More over cost-efficiency calculations will be performed.

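### The trial is sized on live birth per cycle, but the abstract defines the primary outcome per embryo transfer; one denominator, per randomised woman, should serve both

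*Protocol article*

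**What the plan says.** The protocol article gives the live birth rate three denominators.

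- **Sample size and power considerations:** "Live birth rates in FET treatment in the Netherlands are, on average, 20% per cycle". Each woman contributes one cycle, so this is a rate per started cycle, or per woman. For the margin, "a consensus of a MCID of 7,5% was adapted", with no unit of its own. The result is stated as "Using a two-sided alpha of 5% and 80% discriminating capacity we calculated that 1150 patients have to be enrolled in this study".
- **Abstract, Methods and design:** "The primary outcome will be live birth rate per embryo transfer procedure". The sample size is repeated there as "one-sided alpha 2,5%, beta 20%) a total of 1150 patients will be needed".
- **Primary and secondary endpoints:** "The primary endpoint is live birth rate per FET". The next sentence reads "Secondary endpoints are cancellation rate, clinical pregnancy rate, ongoing pregnancy rate (all per FET", so cancellation has the same denominator as the pregnancy rates.

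The Interventions section describes cycles that end without transfer. In NC-FET, if no follicle is visible, ovulation is deemed to have occurred, nothing is thawed and the cycle counts as a drop-out. In AC-FET, raised LH or progesterone with a visible follicle stops thawing and transfer, and after a thin first scan the next step depends on the endometrium at a second scan. The Background gives one cancellation figure, for NC-FET: "5-6% of all patients have insufficient development of the dominant follicle and/or endometrium thickness and treatment has to be cancelled". It says separately that cycles with spontaneous ovulation are usually cancelled, without a rate. Data analysis plans a per-protocol analysis and, beside it, an intention-to-treat analysis, and gives no denominator for either.

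**The concern.** If the primary endpoint is per transfer, a cancelled cycle leaves the denominator. Two things follow.

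First, the denominator is set after randomisation by events that depend on the allocated preparation: spontaneous ovulation and poor follicular or endometrial development in NC-FET, luteinisation or a thin endometrium in AC-FET. The arms compared are then no longer the arms randomised. A difference in cancellation, which is part of what separates the two strategies for a woman starting a cycle, disappears from the primary result.

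Second, the planning rate and the endpoint refer to different quantities. Fewer than 1150 women would be analysed, and if 20% is truly per cycle, the per-transfer rate and its variance would be higher than planned. The stated power would then not describe the analysis carried out.

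**Working it through.** **Inputs from the article:** 20% live birth per cycle, taken as equal in both arms; margin 7.5 percentage points; one-sided 2.5% (equal to two-sided 5%); 80% power; 1:1 allocation; 1150 women, so 575 per arm. **Assumption:** a cancellation share c, equal in both arms. The article gives no total cancellation rate.

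**1. The plan's own figure.** Per arm, n = 2p(1−p)(1.96 + 0.8416)² / 0.075² = 0.32 × 7.849 / 0.005625 = 446.5, so 447 per arm and 894 in total. The stated 1150 does not follow from the stated inputs; it is 256 (29%) more. 894/(1−d) reaches 1150 only at d of about 22%, and the article names no such allowance.

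**2. Power per randomised woman.** Standard error = √(0.32/575) = 0.02359; 0.075/0.02359 = 3.179; power = Φ(3.179 − 1.96) = 88.9%.

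**3. Power per transfer.** With n = 575(1−c) per arm, power = Φ(0.075/√(2p(1−p)/n) − 1.96). There are two readings of the 20%: (a) per cycle as written, so p = 0.20/(1−c) per transfer; (b) already per transfer, so p = 0.20. The margin stays at 7.5 points in both.

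| Cancelled (both arms) | Transfers | Power, reading (a) | Power, reading (b) |
|---|---|---|---|
| 5% | 1092 | 86.0% | 87.3% |
| 6% | 1081 | 85.4% | 86.9% |
| 10% | 1035 | 82.7% | 85.5% |
| 14% | 989 | 79.7% | 83.9% |
| 20% | 920 | 74.8% | 81.2% |
| 25% | 862 | 70.2% | 78.6% |

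Worked line for 14%, reading (a): p = 0.20/0.86 = 0.2326; n = 494.5; standard error 0.0269; 0.075/0.0269 = 2.79; Φ(2.79 − 1.96) = 79.7%. Power crosses 80% at about 13.6% cancellation under (a) and about 22% under (b).

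**4. Margin rescaled too.** If the 7.5 points are also per cycle, the per-transfer margin is 0.075/(1−c). Under reading (a), power is then 89.7% at 10% cancellation, 90.1% at 14% and 90.7% at 20%, so it does not fall.

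**5. What the denominator can hide.** As an illustration only, suppose 20% are cancelled in one arm and 10% in the other, with the same 23.5% live birth rate per transfer. Per started cycle the rates are 0.80 × 23.5% = 18.8% and 0.90 × 23.5% = 21.15%, a difference of 2.35 points. That is about a third of the margin (2.35/7.5 = 0.31), and the per-transfer comparison would show zero.

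**The case against.** The tempting stronger reading is that the trial misses its 80% power. The documents do not support it. The only documented cancellation figure leaves 85–87% per transfer. Even at 14% the range is 79.7% to 83.9%, and the less favourable reading needs 1161 women (998 transfers / 0.86) against 1150, a 1% gap. The loss also depends on converting the rate while holding the margin fixed; convert both and there is none. The surplus of 1150 over 894 may itself be an allowance that the condensed article does not describe. All of this stands. The one limit is that 5–6% is not a total: it covers insufficient development in NC-FET only, so a total above 14% is neither shown nor excluded.

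A second objection is that the denominators may already agree. Because cancellation is listed per FET, and a cancellation rate makes sense only per started cycle, "per FET" could mean per started cycle. That is a fair reading of the endpoints section, but the abstract names the transfer procedure, so the two places still need reconciling.

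Third, an intention-to-treat analysis is already planned. That makes the change small but does not remove the point: the article names the per-protocol analysis first and gives neither analysis a denominator.

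Finally, including untransferred cycles in a non-inferiority trial can dilute a difference that exists among transfers. This is a reason to keep the per-transfer result in view as a secondary analysis, not to leave the primary denominator dependent on events after randomisation.

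A reader might also infer that cancellation is known to differ between the arms. The article gives different reasons by arm and reports a claim of fewer thin-endometrium cancellations with estrogen, but it has no rates to compare.

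**Conclusion.** The mismatch holds: the planning rate is per cycle, the abstract's primary outcome is per embryo transfer, and the endpoints section can be read either way. As the abstract words it, the primary comparison conditions on reaching transfer, which the allocated treatment can influence, and it is not the quantity the trial was sized on.

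A power shortfall is not established. On the stated inputs, power is about 89% per randomised woman. Per transfer it drops materially only at cancellation levels that the article neither reports nor rules out. These figures rest on equal live birth rates in both arms, equal cancellation in both arms and a normal approximation. The correction is worth making because it aligns the endpoint with the design at almost no cost.

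**What to change.** - In the abstract, in Primary and secondary endpoints, and in Data analysis, define the primary endpoint as live birth per randomised woman (per started cycle), with a cancelled cycle counted as no live birth.
- In the sample size section, state that the 20% rate and the 7.5-point margin are both on that denominator. Restate power as about 89% for 1150 women, or show how 1150 was derived, since the stated inputs give 894.
- Report live birth per transfer as a secondary endpoint, next to the cancellation rate by arm.
- If the per-transfer endpoint is kept as primary instead, state the expected total cancellation rate, the per-transfer live birth rate and the scale of the margin, and restate power on those.

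Cost: the per-transfer result loses its primary status, and a few sentences change. The intention-to-treat analysis is already planned, and no extra patients are needed.

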### Hypothesis

The hypothesis to be tested is that there is no significant difference in live birth rates between NC-FET and AC-FET, but that NC-FET is more cost effective. Since the expected low incidence of serious adverse events we expect to find no significant difference based on a type 1 error.

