### Study design

The ANTARCTICA trial is a multi-center, randomized controlled trial, powered to demonstrate non-inferiority of NC-FET in terms of the primary study end point. A recent systemic review of current literature identified no other RCTs addressing this subject. Several retrospective studies have shown discrepant findings but pooling of the data indicated no difference in pregnancy rates between NC-FET and AC-FET. Since our hypothesis is that significant difference in the primary study endpoint will not be observed, but a difference in cost-efficacy in favour of the NC-FET will be demonstrated, a non-inferiority design is appropriate. The research team is blinded for the result of the randomization (Figure
1).

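### The only written null hypothesis runs opposite to the stated aim: rejecting it shows AC-FET non-inferior to NC-FET and leaves the claim about NC-FET untested

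*Protocol article*

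**What the plan says.** The Study design section of the protocol article states that the trial is "powered to demonstrate non-inferiority of NC-FET in terms of the primary study end point". It gives the reason: equal live birth rates are expected, and because "a difference in cost-efficacy in favour of the NC-FET will be demonstrated, a non-inferiority design is appropriate". The Hypothesis section takes the same line, expecting that "there is no significant difference in live birth rates between NC-FET and AC-FET, but that NC-FET is more cost effective". NC-FET is thus the treatment that must be shown not to lose live births, and AC-FET is what it is compared with. No section names a reference arm; AC-FET as reference is inferred from these statements.

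The section on sample size and power considerations sets the margin ("a consensus of a MCID of 7,5% was adapted") and the expected rate ("Live birth rates in FET treatment in the Netherlands are, on average, 20% per cycle"). It then describes "a one sided hypothesis test with a 0.025% significance level" and completes that sentence "with a null hypothesis of AC-FET being inferior to NC-FET".

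The Data analysis section names the analysis populations and the regression covariates. It gives no signed difference, no comparison with the margin and no confidence-limit rule.

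**The concern.** A non-inferiority test is one-sided and not symmetric. To conclude that NC-FET is non-inferior, the null to reject is that NC-FET is worse than AC-FET by at least the margin. The sample-size section exchanges the arms. Rejecting its null supports a different statement, that AC-FET is not worse than NC-FET by the margin, and does not bear on whether NC-FET loses live births.

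The primary conclusion is at stake. An analyst who follows the sample-size section compares the wrong limit of the interval with the margin, and can report success when NC-FET is worse by a difference that the protocol itself calls clinically important. The cost argument for NC-FET rests on the claim that this test would not examine. With two opposite directions on record, the direction could also be chosen after the data are seen.

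**Working it through.** **Inputs.** Live birth rate 20% and margin 7.5%, read as absolute percentage points (sample-size section). Allocation 1:1 (Randomization), so 1150 / 2 = 575 per arm. One-sided 2.5% level and 80% power from the abstract ("one-sided alpha 2,5%, beta 20%) a total of 1150 patients will be needed"). The sample-size section prints 0.025%; I use the abstract's 2.5%, which agrees with the two-sided 5% given later in the sample-size section. NC-FET rates other than 20% are illustrative assumptions of this review.

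**The plan's own figure.** With the same rate p in both arms, n per arm = (1.960 + 0.842)² × 2p(1 − p) / margin² = 7.849 × 0.32 / 0.005625 = 446.5, so 447 per arm and 894 in total. The stated 1150 is not reproduced, which is a separate matter. What counts here is that the formula does not change when the arms are exchanged, so the sample size carries no information about direction.

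**The two tests at 575 per arm.** Let SE = √{[p_NC(1 − p_NC) + p_AC(1 − p_AC)] / 575}.

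- Null as written (AC-FET inferior): probability of rejection ≈ Φ[(p_AC − p_NC + 0.075) / SE − 1.96].
- Null matching the aim (NC-FET inferior): probability of rejection ≈ Φ[(p_NC − p_AC + 0.075) / SE − 1.96].

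With p_AC = 0.20:

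- p_NC = 0.20: SE = √(0.32 / 575) = 0.02359. Both tests give Φ(0.075 / 0.02359 − 1.96) = Φ(1.22) = 0.889.
- p_NC = 0.125: SE = √(0.269375 / 575) = 0.02164. As written, Φ(0.15 / 0.02164 − 1.96) = Φ(4.97) ≈ 1.00. Matching the aim, Φ(−1.96) = 0.025.
- p_NC = 0.275: SE = √(0.359375 / 575) = 0.02500. As written, Φ(−1.96) = 0.025. Matching the aim, Φ(0.15 / 0.025 − 1.96) = Φ(4.04) ≈ 1.00.

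**Exact check.** Enumerating all pairs of outcomes of two binomials with 575 per arm, using Wald 95% limits and AC-FET at 20%, gives:

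| True NC-FET rate | Null as written rejected | Null matching the aim rejected |
|---|---|---|
| 12.5% | about 100% | 2.6% |
| 15% | about 100% | 20.1% |
| 17% | 99.6% | 50.4% |
| 20% | 88.9% | 88.9% |
| 23% | 46.0% | 99.1% |
| 27.5% | 2.5% | about 100% |

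**One set of results read both ways.** Suppose 86 of 575 live births with NC-FET (15.0%) and 115 of 575 with AC-FET (20.0%). NC minus AC is −5.0 points with SE 2.23 points, so the 95% interval is −5.0 ± 1.96 × 2.23, or −9.4 to −0.7. The lower limit is below −7.5, so NC-FET is not shown to be non-inferior. For AC minus NC the interval is 0.7 to 9.4. Its lower limit is above −7.5, so the null as written is rejected and the trial would report success.

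**The case against.** The strongest reply is that this is a slip in a paragraph about sample size and not the trial's decision rule. The same sentence prints a significance level of 0.025% where the abstract has 2.5%, so it was not carefully proofread. The Study design section is explicit about NC-FET and gives a reason, so a reader can infer the intended direction. The full protocol or a statistical analysis plan may state the rule correctly. A two-sided 95% interval would show both limits, so a loss with NC-FET would be visible in the report. Finally, the extreme probabilities follow from reversing any non-inferiority test, and the unequal rates are not design assumptions.

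Part of this stands. A slip is plausible, the estimate and its interval are the same in either direction, and the unequal rates only illustrate. The rest does not remove the problem. The reversed null is stated, not left out, so any later document must contradict one of the two sections. The article nowhere says that both limits will be read against the margin; it calls the test one-sided, and the two-sided 5% enters only the sample-size calculation. The abstract, the Discussion and the Hypothesis section speak of the live birth rates not differing, which gives no direction.

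**Conclusion.** The concern holds. The Study design and sample-size sections of the protocol article contradict each other on the direction of the primary test, and nothing else in the article settles it. Followed as written, the test would succeed almost surely if NC-FET lost the full 7.5 points, where the matching test would succeed 2.6% of the time. It would also almost always fail (2.5% success) if NC-FET were 7.5 points better.

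These figures assume 575 analysed patients per arm, AC-FET at 20%, an absolute margin, a one-sided 2.5% level and Wald limits. The contradiction depends on none of them. Because the direction determines the primary conclusion, this must be corrected.

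**What to change.** Rewrite the null hypothesis in the sample-size section to agree with the Study design section, and carry the same rule into the analysis plan:

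- H0: LBR(NC) − LBR(AC) ≤ −7.5 percentage points.
- H1: LBR(NC) − LBR(AC) > −7.5 percentage points.
- NC-FET is declared non-inferior if the lower limit of the two-sided 95% confidence interval for NC minus AC lies above −7.5 points.

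The change should be made and dated before anyone sees outcomes by arm, so that the direction cannot depend on the results. It costs one sentence. The sample size does not change, because the calculation takes 20% in both arms and is the same in either direction, and the conduct of the trial is not affected.

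### The one-sided test level is printed as 0.025% where 2.5% applies elsewhere, and 1150 patients does not follow from the inputs it is attributed to (they give 894)

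*Protocol article*

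**What the plan says.** The significance level appears three times in the protocol article.

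- Abstract, Methods and design: "one-sided alpha 2,5%, beta 20%) a total of 1150 patients will be needed". The same sentence bases the number on a 20% live birth rate and a minimal clinically important difference of 7.5%.
- Sample size and power considerations, one sentence: a "one sided hypothesis test with a 0.025% significance level". The null attached to it makes the artificial cycle (AC-FET) the inferior arm.
- Same section, next sentence: "Using a two-sided alpha of 5% and 80% discriminating capacity we calculated that 1150 patients have to be enrolled in this study".

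The other inputs are consistent throughout. For the event rate: "Live birth rates in FET treatment in the Netherlands are, on average, 20% per cycle". For the margin: "a consensus of a MCID of 7,5% was adapted". Randomization gives 1:1 allocation, and each woman contributes one cycle. Study design says the trial is "powered to demonstrate non-inferiority of NC-FET in terms of the primary study end point", where NC-FET is the natural cycle.

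Neither the abstract nor the sample size section mentions an allowance for cancelled cycles or drop-out.

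**The concern.** Two figures that the trial relies on look wrong as written.

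The first is the decision threshold. The sample size section attaches 0.025% to the one-sided hypothesis test, which is the test that decides non-inferiority. A reader who takes it literally has a criterion 100 times stricter than the one in the abstract.

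The second is the sample size. Both places present 1150 as the product of the rate, margin, level and power. If it is not, a reader cannot tell what 1150 stands for. It could be women analysed, with power well above 80%, or women enrolled, of whom a sizeable share is expected not to contribute. This matters because the data analysis section puts a per-protocol analysis first, and the interventions section describes cycles in both arms that end without transfer. The loss the trial can absorb depends on which meaning was intended. The Discussion also attributes the relatively high number of patients to the 7.5% margin, but on the stated inputs that margin accounts for only part of it.

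**Working it through.** **Inputs from the article:** live birth 20%, taken as equal in both arms; margin 0.075; power 80% (z = 0.8416); 1:1 allocation; one cycle per woman, so no inflation for repeat cycles.

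**Formula (unpooled variance):** n per arm = (z_alpha + z_beta)² × 2p(1 − p) / margin², with 2p(1 − p) = 2 × 0.2 × 0.8 = 0.32 and margin² = 0.005625.

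**Step 1. Attempt to reproduce 1150 at one-sided 2.5% (z = 1.960).** Two-sided 5% has the same critical value.

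n = (1.960 + 0.8416)² × 0.32 / 0.005625 = 446.5, so 447 per arm and 894 in total. The stated 1150 is 256 more (1150/894 = 1.29).

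**Step 2. Power if all 1150 are analysed (575 per arm).**

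SE = √(0.32/575) = 0.02359, and 0.075/0.02359 = 3.179. Power = Φ(3.179 − 1.960) = 0.889.

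**Step 3. The level as printed, 0.025% (0.00025, z = 3.481).**

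Power at 575 per arm = Φ(3.179 − 3.481) = 0.38. For 80% power, n = (3.481 + 0.8416)² × 0.32 / 0.005625 = 1062.9, so 1063 per arm and 2126 in total.

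**Step 4. Other standard readings.**

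| Reading | Total |
|---|---|
| Non-inferiority, one-sided 2.5%, 80% power | 894 |
| Same, Farrington-Manning | 900 |
| Same, continuity-corrected | 946 to 948, depending on rounding |
| Two-sided 5% superiority, 20% v 27.5% | 1010 (1062 continuity-corrected) |
| Two-sided 5% superiority, 20% v 12.5% | 758 (810 continuity-corrected) |
| Equivalence (TOST), 2.5% per side, 80% power | 1196 |
| Non-inferiority, one-sided 2.5%, 90% power | 1196 |
| Non-inferiority, one-sided 0.025%, 80% power | 2126 |

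None of these is within 3% of 1150 (1116 to 1184). The matches found all need an input that the article does not state, such as a one-sided level of 1.25% with continuity correction (1136).

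**Step 5. Loss needed to connect 894 with 1150.**

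1 − 894/1150 = 22.3%. The only cancellation figure in the article is 5-6%, given in the Background for natural cycles with insufficient follicle or endometrium development. Applying 6% to both arms gives 894/0.94 = 951.

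**The case against.** The strongest reply has four parts.

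*The levels hardly conflict.* One-sided 2.5% and two-sided 5% are one threshold for non-inferiority, and 0.025% is most plausibly 0.025 with a stray percent sign. This stands. A reader might infer three competing levels, but there are two equivalent statements and one misprint, and the intended level can be recovered from the other two. The misprint still needs correcting because it is the level printed for the one-sided test itself.

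*The 1150 may include a loss allowance.* The text says that 1150 have to be enrolled, whereas 894 is a number analysed. The design has loss built in. Natural cycles with no visible follicle are drop-outs, artificial cycles with raised LH or progesterone get no transfer, and the Background describes cancellation after spontaneous ovulation in addition to the 5-6%. The full protocol may well hold an allowance of about 22%, and its absence from an article is not in itself a fault. This stands as a possible explanation. It does not rescue the wording, because both places derive 1150 from rate, margin, level and power alone.

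*The error is in the safe direction.* This stands. At one-sided 2.5%, power is at least 80% for any loss up to about 22%. The documents do not support reading the mismatch as underpowering, or as proof that the stated level and power are not those of the design.

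*Nobody would test at 0.025%.* Probably so, since the next sentence says two-sided 5%. Even taken literally, 38% power means failure in about 62% of trials if the arms are truly equal. That is a serious shortfall but not near-certain failure.

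**Conclusion.** The point holds in two limited parts, and both should be corrected.

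First, 0.025% is a misprinted decision threshold, too strict by a factor of 100. At that level 1150 patients would give about 38% power. The null in the same sentence also makes AC-FET the inferior arm, whereas Study design sets out to show non-inferiority of NC-FET. With equal rates this does not alter the sample size, but correcting the percentage alone would leave the wrong test defined.

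Second, 1150 cannot be reproduced from its stated basis. The inputs give 894, so 1150 is 29% larger. It means about 89% power if all are analysed, or 80% with up to about 22% not contributing.

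These figures assume a 20% rate in both arms, an absolute margin of 7.5 points, equal allocation and a normal approximation with unpooled variance. Farrington-Manning or a continuity correction moves 894 to between 900 and 948, which does not close the gap. Whether a loss allowance was used cannot be settled from the article.

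**What to change.** In the sample size section:

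1. Replace 0.025% with 2.5%, and use one level throughout the article: one-sided 2.5%, equivalently a two-sided 95% confidence interval.
2. Reword the null in that sentence to match Study design: the live birth rate with NC-FET is lower than with AC-FET by 7.5 percentage points or more.
3. Restate the size: 894 women analysed give 80% power; 1150 enrolled give 89% if all are analysed, or 80% after the loss allowance actually used. Give that allowance. If none was used, state the power as 89%.

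Make the abstract agree. The cost is a few corrected figures and one clarifying sentence, with no change in enrolment.
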